## Abstract

**Introduction:**

Acute exacerbation of chronic obstructive pulmonary disease (AECOPD) may cause stress-induced transient acute cardiac dysfunction through myocardial stunning, in the form of exacerbation-triggered Takotsubo syndrome (referred to as Takotsubo stunning). Although prior studies suggest an association between AECOPD and transient cardiac dysfunction, existing evidence is limited to retrospective cohorts, case reports and expert consensus. Therefore, the incidence and clinical impact of Takotsubo stunning with acute heart failure (AHF) during AECOPD remain unknown and may be overlooked due to overlapping clinical symptoms. Cardiac Assessment and Takotsubo-stunning among COPD-exacerbations in-Hospital (CATCH study) aims to determine the incidence of Takotsubo stunning during AECOPD and to evaluate its clinical implication.

**Methods and analysis:**

CATCH is a prospective observational cohort study enrolling adults (≥18 years) admitted for AECOPD at Sahlgrenska University Hospital (Gothenburg, Sweden). Participants with chronic left ventricular systolic dysfunction (left ventricular ejection fraction <50%), pre-existing chronic regional wall motion abnormalities (RWMA) or prior type 1 myocardial infarction are excluded. Following informed consent, participants undergo echocardiographic screening for RWMA and/or systolic left ventricular dysfunction. Screening-positive patients have follow-up echocardiography at 24 hours (±6) and 30 days (±48 hours). Those with reversible dysfunction constitute the CATCH case group, while screening-negative participants serve as controls. Additional assessments include ECG, chest X-ray, N-terminal pro-B-type natriuretic peptide blood analysis and COPD severity. Primary outcomes include the incidence of reversible RWMA or left ventricular dysfunction (proxy for Takotsubo stunning) and in-hospital clinical signs of AHF (Killip class >1). A sample size of 150 patients is required for detecting AHF differences (α=0.05, 80% power).

**Ethics and dissemination:**

The study received ethical approval from the Swedish Ethical Review Authority. All participants provided written informed consent. Results will be disseminated through peer-reviewed journals and scientific meetings.

**Registration details:**

The CATCH study is registered at ClinicalTrials.gov (NCT06597331). The reference number for ethical approval is 2024-02071-01 (with addenda 2024-05448-02 and 2025-05861-02).

WHAT IS ALREADY KNOWN ON THIS TOPICSevere acute exacerbation of chronic obstructive pulmonary disease (AECOPD) is associated with increased short-term risk of acute cardiovascular events. Retrospective cohorts, case series and expert consensus have indicated an association between AECOPD and stress-induced myocardial stunning, manifesting as exacerbation-triggered Takotsubo syndrome (referred to as Takotsubo stunning in the protocol), which is characterised by acute heart failure that may further aggravate the AECOPD episode.WHAT THIS STUDY ADDSCardiac Assessment and Takotsubo-stunning among COPD-exacerbations in-Hospital (CATCH study) is the first study to systematically test the association between AECOPD and Takotsubo stunning in a prospective cohort.HOW THIS STUDY MIGHT AFFECT RESEARCH, PRACTICE OR POLICYThe CATCH study will determine the true association between AECOPD and Takotsubo stunning, which will impact AECOPD management.

## Introduction

 This paper describes the protocol of the Cardiac Assessment and Takotsubo-stunning among COPD-exacerbations in-Hospital (CATCH study), investigating to what extent acute exacerbation of chronic obstructive pulmonary disease (AECOPD) triggers cardiac dysfunction through stress-induced myocardial stunning.

AECOPD may cause acute heart failure (AHF) due to stress-induced myocardial stunning, which is probably underdiagnosed (or possibly undiagnosed) in clinical routine.^1 2^ Myocardial stunning was originally defined as temporary cardiac mechanical dysfunction that persists after resolution of ischaemia, with the absence of irreversible histological damage,^3^ and has later been shown to also occur outside of the ischaemic setting.^4^ Elements of myocardial stunning are associated with several conditions, such as after acute myocardial infarction, postcardiac arrest and in the setting of acute myocarditis. However, the Takotsubo syndrome (TS) likely represents a relatively pure form of myocardial stunning, making this condition particularly attractive for investigating stunning per se.^5^

TS is a heart failure syndrome associated with severe emotional or physical stress predominately affecting females (>90% females) in the postmenopausal ages. TS is characterised by rapid onset of reversible left ventricular systolic dysfunction, typically affecting the apical parts of the left ventricle (with full recovery within days to weeks in most cases). Although the pathophysiology of TS is incompletely understood, catecholamine excess (‘catecholaminergic storm’) is thought to play a large role, leading to cardiac microvascular dysfunction and/or direct catecholamine toxicity on the cardiomyocyte, resulting in myocardial stunning.^3 5 6^

Because of its association with stress, TS is sometimes termed ‘stress cardiomyopathy’. However, ‘stress cardiomyopathy’ was first described in 1980,^7^ before the first description of TS in 1990.^8 9^ Furthermore, left ventricular dysfunction in the setting of neurological disease or cerebrovascular insult was described as early as 1908 and later termed neurogenic stunned myocardium, a condition similar to TS, leading some authors to conclude that these entities likely constitute the same syndrome.^10^ The link between these conditions is the association between emotional or physical stressors, leading to acute cardiac dysfunction, probably through myocardial stunning.

Acute pulmonary conditions constitute over one-fifth of all physical triggers of TS and are associated with a more severe in-hospital course and worse long-term outcome, compared with patients with TS without acute pulmonary conditions.^1 11^ There are reports describing patients experiencing frequently recurrent TS triggered by AECOPD,^12 13^ and COPD is significantly over-represented among patients with TS compared with the general population.^14^ Furthermore, patients with COPD hospitalised for TS have a higher incidence of cardiogenic shock, longer length of stay and higher in-hospital mortality compared with those without COPD.^15^ Concurrent respiratory disease such as AECOPD complicates the diagnosis of TS, since the cardiac condition may be masked by the pulmonary symptoms.^14^ Also, the respiratory symptoms may be further exacerbated by (perhaps undiagnosed) myocardial stunning resulting in heart failure.^1 11 14 15^

The term ‘Takotsubo-stunning’ has been suggested for the myocardial stunning that occurs in TS.^16^ This term will also be used in this protocol, referring to the myocardial stunning that occurs in TS. The association between AECOPD and Takotsubo stunning has not been systematically evaluated in a prospective cohort. The purpose of the CATCH study is to improve our understanding of the impact of Takotsubo stunning in patients with AECOPD, thereby potentially enhancing the quality of care.

## Methods and analysis

### Research aim

To investigate the extent to which AECOPD triggers Takotsubo stunning in admitted patients, and to evaluate its subsequent effect on clinical outcomes.

### Objectives and outcomes

#### Primary objectives

To determine the incidence of reversible left ventricular systolic dysfunction (as a proxy for Takotsubo stunning) in patients hospitalised for AECOPD at Sahlgrenska University Hospital (Gothenburg, Sweden).To investigate in-hospital clinical manifestations of AHF (defined as Killip class >1, table 1) in patients with signs of Takotsubo stunning versus those without, among patients hospitalised for AECOPD at Sahlgrenska University Hospital.

**Table 1 T1:** Killip classification of acute left-sided heart failure, based on clinical signs supported by chest imaging

Killip class I	No clinical/radiological signs of heart failure.
Killip class II	Clinical and radiological signs of heart failure but not pulmonary oedema (distinct bilateral rales or crackles over lungs suggesting interstitial fluid supported by interstitial fluid on chest X-ray*).
Killip class III	Clinical picture of frank pulmonary oedema supported by radiological* signs.
Killip class IV	Cardiogenic shock or hypotension (measured as systolic blood pressure lower than 90 mm Hg) and evidence of peripheral vasoconstriction (oliguria, cyanosis or sweating).

* Pulmonary ultrasound may be used to confirm Killip class.

#### Secondary objectives

The secondary objectives include comparisons between patients with AECOPD with and without evidence of Takotsubo stunning. These analyses will be conducted in a hypothesis-generating framework to present new possible mechanistic pathways and clinical associations, focusing on the following variables:

In-hospital and 1-year all-cause mortality, in-hospital complications (acute myocardial infarction, stroke, pulmonary embolism (PE), respiratory failure, clinical deterioration leading to intensive care unit admission) and length of hospital stay.ECG (ST elevation, ST depression, QT prolongation, T-wave inversion).N-terminal pro-B-type natriuretic peptide (NT-proBNP) in plasma.Presenting symptoms (prevalence of chest pain, severity of dyspnoea).Echocardiographic signs of right ventricular strain.

#### Tertiary objectives

The tertiary objectives include investigations within three distinct groups of AECOPD: (1) patients with evidence of Takotsubo stunning, (2) patients without evidence of Takotsubo stunning and (3) the overall cohort, including both patients with and without Takotsubo stunning. In accordance with the secondary objectives, these analyses will also be conducted within a hypothesis-generating framework.

Concordance between echocardiography, chest X-ray and NT-proBNP in displaying signs of heart failure.Prevalence of right ventricular pathology.Prevalence of diastolic dysfunction.The association between NT-proBNP and in-hospital outcome.The association between Killip classification and in-hospital outcome.

### Study design overview

CATCH is a prospective observational cohort study of patients admitted to Sahlgrenska University Hospital for AECOPD. COPD is defined as a documented physician diagnosis of COPD in the hospital or primary care medical record. AECOPD is defined according to the 2024 Global Initiative for Obstructive Lung Disease (GOLD) report as: increased dyspnoea and/or cough and sputum that worsens in <14 days which may be accompanied by tachypnoea and/or tachycardia and is often associated with increased local and systemic inflammation caused by infection, pollution or other insult to the airways.^17 18^ Patients meeting all inclusion criteria and no exclusion criteria are eligible for inclusion and screening for echocardiographic signs of regional wall motion abnormality (RWMA) and/or left ventricular systolic dysfunction. Inclusion takes place from Monday to Friday, and each patient can be included only once; repeat admissions for AECOPD will not lead to reinclusion.

### Study population and eligibility criteria

#### Inclusion criteria

Adult patients (≥18 years old) admitted to a hospital ward for AECOPD.Inclusion within 72 hours of admission.Written informed consent (IC).

#### Exclusion criteria

Prior documented type 1 acute myocardial infarction or documented pre-existing chronic RWMA or reduced left ventricular ejection fraction (LVEF <50%).Expected inability to comply with the protocol (eg, dementia).Previously included in the CATCH study during a prior event with admission for AECOPD.

### Cardiac screening

After IC, patients are screened with echocardiography (following the algorithm in figure 1) for signs of RWMA and/or left ventricular systolic dysfunction (standard clinical protocol) at the Department of Clinical Physiology at Sahlgrenska University Hospital. The echocardiographic examinations are performed by experienced cardiac sonographers and analysed by experienced clinical physiologists. Negative and positive screening will be defined as follows:

Positive=presence of any RWMA and/or left ventricular systolic dysfunction (LVEF <50%).

**Figure 1 F1:**
[figure not shown]
Screening algorithm. CATCH, Cardiac Assessment and Takotsubo-stunning among COPD-exacerbations in-Hospital; COPD, chronic obstructive pulmonary disease; RWMA, regional wall motion abnormality.

Negative=absence of RWMA and no left ventricular systolic dysfunction (LVEF ≥50%).

For patients with a positive screening result, echocardiography will be repeated after 24 (±6) hours and at 30 days (±48 hours). Within the screening-positive group, patients who demonstrate reversibility on repeat echocardiography will constitute the CATCH case group (Takotsubo stunning group), provided that no alternative cause of transient cardiac dysfunction has been identified (according to diagnostic criteria for Takotsubo^16 19^). Reversibility will be defined as normalisation or significant improvement in left ventricular systolic function, indicated by resolution of left ventricular akinesia/hypokinesia and/or improved LVEF ≥10 percentage points.

Cardiac dysfunction detected through study screening will be investigated based on clinical findings and symptoms as per clinical routine, to address alternative causes to Takotsubo stunning. For patients with ongoing or easily provoked chest pain, timely coronary angiography is mandatory to exclude coronary artery occlusion. To exclude or confirm other causes, such as myocarditis or chronic coronary syndromes, cardiac MRI or myocardial perfusion scintigraphy, respectively, may be used according to clinical routine. Hence, in cases with reversible left ventricular dysfunction, Takotsubo stunning will be validated based on clinical investigation together with diagnostic criteria for TS.^19^

If patients within the screening-positive group do not display reversibility by day 30±48 hours (or through further assessment during clinical routine follow-up within 6 months, figure 1), the RWMA and/or left ventricular systolic dysfunction will be considered persistent (ie, fulfilling exclusion criteria unknown at time of inclusion) and the patient will be excluded from analysis.

Patients who turn out negative in screening will constitute the CATCH control group.

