#### Secondary outcomes

In-hospital 3-point major adverse cardiac events (MACE): non-fatal myocardial infarction, non-fatal stroke or cardiovascular death (according to hospital medical chart).Admission to intensive care unit (according to hospital medical chart).In-hospital all-cause death (according to hospital medical chart).Respiratory failure, acute or acute on chronic (hypercapnia with acidosis, PaCO_2_ >6.0 and pH <7.35, according to lab values in hospital medical chart).ST elevation, ST depression, QT prolongation, T-wave inversion on ECG (ECG at admission and inclusion).Level of NT-proBNP (obtained at admission and inclusion).One-year all-cause and cardiovascular death (Swedish Cause of Death Register, National Board of Health and Welfare).

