### Statistical plan and sample size

Inclusion is planned over approximately 3 years to estimate the cumulative incidence of Takotsubo stunning in patients hospitalised for AECOPD. The primary analysis will assess the association between a positive screening result and clinical manifestations of AHF using multivariable logistic regression. The model will adjust for relevant baseline confounders, with a significance threshold of α=0.05.

For the primary analysis, the required sample size is estimated at 150 patients, assuming a 1:10 ratio of positive to negative screening results. In previous research randomly investigating the correlation between clinical and echocardiographic signs of heart failure, clinical heart failure was present in approximately 50% of patients with echocardiographic left ventricular systolic dysfunction (LVEF <40%).^23^ Given the higher cut-off for systolic dysfunction in CATCH (LVEF <50%) and inclusion of newly detected RWMA as positive screening (ie, also in absence of reduced LVEF), together with the exclusion of patients with prior type 1 myocardial infarction or known persistent systolic dysfunction, we conservatively estimate the proportion of clinical heart failure in the positive screening group to approximately 30%. Accordingly, our sample provides 80% power to detect a difference in the incidence of clinical signs of AHF between the groups, assuming 30% in the positive screening group and 5% in the negative screening group with α=0.05.

Secondary and tertiary outcomes will be analysed using linear regression for continuous outcomes and logistic regression for dichotomous outcomes, in both unadjusted and adjusted models. A Cox proportional hazards model adjusted for baseline confounders will be applied to analyse 1-year mortality. These analyses are considered explanatory or hypothesis generating. Results will be reported as effect estimates with 95% CIs and unadjusted p values, with false discovery rate correction applied to account for multiple comparisons.^24^

Unadjusted and adjusted analyses (including covariates age and sex) will be presented as separate models. A sample size of 150 patients, with an assumed 1:10 ratio of positive to negative screening results, translates to a total number of 15 events. Given the relatively low number of expected events, all further adjustment will include only clinically meaningful covariates and will be presented as separate models.

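### Case status requires a later echo showing recovery, while controls are fixed at day 0, so the case-versus-control mortality comparisons lose early deaths from the exposed group only

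*Protocol article*

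**What the plan says.** **How the groups are formed (Protocol article, Cardiac screening).** Screening-positive patients have repeat echocardiography at 24 (±6) hours and at 30 days (±48 hours). Of these, "patients who demonstrate reversibility on repeat echocardiography will constitute the CATCH case group (Takotsubo stunning group), provided that no alternative cause" of the transient dysfunction has been found. The remaining positives are covered by one rule: "If patients within the screening-positive group do not display reversibility by day 30±48 hours", or in routine clinical follow-up within 6 months, the dysfunction is deemed persistent "and the patient will be excluded from analysis". The text has no separate provision for a positive who dies, or has no repeat echo, before reversibility could be shown. Screening-negative patients become controls at once, with no further condition.

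**What is compared.** Secondary objectives contrast patients with and without evidence of stunning on in-hospital and 1-year all-cause mortality, among other outcomes. Secondary outcomes add in-hospital death, intensive care admission and "In-hospital 3-point major adverse cardiac events (MACE): non-fatal myocardial infarction, non-fatal stroke or cardiovascular death". Postdischarge follow-up registers deaths within 1 year of inclusion. Statistical plan and sample size states: "A Cox proportional hazards model adjusted for baseline confounders will be applied to analyse 1-year mortality". It mentions neither a landmark nor time-dependent exposure.

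**The primary heart-failure comparison is worded in two ways.** Primary objectives contrast patients with signs of stunning against those without. Statistical plan and sample size instead takes a positive screening result as the exposure, and bases 80% power on 150 patients at a 1:10 ratio with rates of 30% and 5%.

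**The concern.** A case must be alive and examined again at some point after inclusion; a control need not be. When both are followed from inclusion, a case confirmed at day 30 contributes 30 days in which death was impossible by definition. A positive who dies in those days without shown recovery is in neither group. This is immortal-time bias combined with selection on later outcome, and it acts on one side only.

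In-hospital death is the sharpest instance. A positive who dies in hospital before day 30 can count as a case only if the 24-hour echo, or an unscheduled clinical one, had already shown recovery. The cardiovascular-death part of MACE is affected in the same way.

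Covariate adjustment and false-discovery-rate correction do not remove the bias. At stake is the study's second aim, the effect of stunning on clinical outcomes: a real excess of deaths could shrink or disappear, and a null could look protective.

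**Working it through.** **1. The plan's own figure.** Inputs from Statistical plan and sample size: N = 150, ratio 1:10, 30% versus 5%, α = 0.05 (taken as two-sided).

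- Positives 150/11 = 13.6; negatives 136.4.
- Pooled rate (13.6 × 0.30 + 136.4 × 0.05)/150 = 0.0727.
- Null SE = √[0.0727 × 0.9273 × (1/13.6 + 1/136.4)] = 0.0738.
- Alternative SE = √[0.21/13.6 + 0.0475/136.4] = 0.1255.
- z = (0.25 − 1.96 × 0.0738)/0.1255 = 0.84, so power = 0.80.

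The stated 80% reproduces, provided that every screening-positive patient is analysed.

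**2. Timing of classification and of counting.**

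| | Exposed (cases) | Controls |
|---|---|---|
| Group fixed | When reversibility is shown: 24 h, day 30, or up to 6 months | Day 0 |
| Must survive to be classified | Yes | No |
| Deaths counted from | Inclusion | Inclusion |

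**3. Size for 1-year mortality.** The documents give no death risks, so these are assumptions: the same true risk in both groups, m30 at 30 days and m1 at 1 year, and every case first confirmed at day 30.

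- Apparent case risk = (m1 − m30)/(1 − m30).
- Apparent hazard ratio, as the ratio of 1-year cumulative hazards = ln(1 − apparent case risk)/ln(1 − m1).

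| m30 | m1 | Apparent case risk | Apparent HR (truth 1.0) |
|---|---|---|---|
| 5% | 20% | 0.15/0.95 = 15.8% | 0.77 |
| 8% | 25% | 0.17/0.92 = 18.5% | 0.71 |
| 10% | 30% | 0.20/0.90 = 22.2% | 0.70 |

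**4. Check without fixing the confirmation day.** Let q be the true death risk in the exposed and f the share of their deaths that precede shown reversibility. Observed risk = q(1 − f)/(1 − qf).

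- True relative risk 1 (q = 5% or 10%): the observed value is about 0.76 for f = 25%, 0.51 to 0.53 for f = 50%, and 0.26 to 0.27 for f = 75%.
- True relative risk 2 (10% versus 5%, or 20% versus 10%): 1.54 to 1.58, 1.05 to 1.11, and 0.54 to 0.59.

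The direction is the same throughout. The size depends on f, which the documents do not give.

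**5. Primary heart-failure analysis, if the exclusion is applied to it.** Start from 14 positives and 136 negatives (power 0.805).

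- Losing 1, 2, 3 or 5 positives with the rate still 30% gives power 0.789, 0.771, 0.751 or 0.705.
- If 10% to 30% of positives are excluded and 50% to 70% of those had heart failure (assumed), the analysed rate is (0.30 − e × r)/(1 − e), where e is the excluded share and r their heart-failure rate. It runs from 27.8% (e = 0.1, r = 0.5; power 0.74) to 12.9% (e = 0.3, r = 0.7; power 0.26).
- If no positive is excluded, the stated 80% stands.

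**6. Incidence.** With all 150 in the denominator, each unassessable positive moves the estimate by 1/150 = 0.67 percentage points, depending on how that patient is counted.

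**The case against.** **Reversibility defines the condition, and the outcomes are exploratory.** Both are true. A contrast by screening result would admit persistent dysfunction, which the protocol means to exclude. But the case definition can stand while follow-up time is aligned, and an exploratory label does not make a biased hazard ratio interpretable.

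**The exclusion is aimed at unrecognised chronic disease, not deaths.** That is its stated rationale, and the flow figure it cites is not shown. As worded, however, it reaches every positive without shown reversibility. Even if deaths were handled separately, such patients could not become cases.

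**The size is speculative.** This stands. The hazard ratios of 0.77 to 0.70 need every case to be confirmed at day 30, whereas an echo is scheduled at 24 hours and the Introduction expects recovery in days to weeks. Cases confirmed only in later routine follow-up would be more affected. With 14 positives and an assumed 5% to 10% 30-day mortality, only 0.7 to 1.4 deaths are expected before day 30.

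Four stronger readings are tempting and are not supported:

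- *The primary heart-failure analysis is shown to lose its severest events.* The statistical plan already uses the day-0 result. Whether the exclusion also applies is unresolved, and a patient in cardiogenic shock who later recovers still counts.
- *Infarctions are removed from cases.* The text says "timely coronary angiography is mandatory to exclude coronary artery occlusion" for patients with ongoing or easily provoked chest pain, and mentions myocarditis and chronic coronary syndromes. A later infarction in a confirmed case still counts towards MACE.
- *Incidence counts the dead as not stunned.* They are excluded from analysis, so whether they remain in the denominator is unclear.
- *The Introduction shows that the lost events typify stunning.* Its statement that "patients with COPD hospitalised for TS have a higher incidence of cardiogenic shock, longer length of stay and higher in-hospital mortality" compares Takotsubo patients with and without COPD, not stunned and unstunned exacerbations.

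**Conclusion.** The point holds for the secondary comparisons of in-hospital and 1-year mortality and for the cardiovascular-death part of MACE. Followed as written, the plan loses deaths before shown reversibility from the exposed group only, so stunning appears safer than it is. The direction follows from the definitions; the size is unknown. A true hazard ratio of 1.0 appearing as 0.77 to 0.70 is an illustration towards the upper end. It rests on assumed mortality and on day-30 confirmation throughout, and early recovery would reduce it.

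For the primary heart-failure analysis the finding is an inconsistency, not a demonstrated bias. The power figure assumes that all of about 14 positives are analysed, the screening section excludes some after inclusion, and the objective names a different contrast.

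**What to change.** 1. Do not classify death or a missing repeat echo as persistent dysfunction. Keep these patients as a separate category: screening-positive, reversibility not assessable. Report the incidence with bounds, counting them first as non-reversible and then as reversible.
2. Analyse 1-year mortality for cases versus controls from a day-30 landmark applied to both groups, or with case status as a time-dependent covariate. The second option also accommodates cases confirmed only in later routine follow-up.
3. Compare in-hospital death, intensive care admission and MACE by day-0 screening result alongside any case-versus-control comparison.
4. State that the primary heart-failure analysis by screening result keeps every screening-positive patient, without the post-inclusion exclusion. Present the reversible-only contrast as a sensitivity analysis, and align the wording of Primary objectives, Cardiac screening, and Statistical plan and sample size.

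**Cost.** No new data collection is needed. Study status reports 56 of 150 patients enrolled by April 2026, with analysis planned after inclusion ends, so the change can precede any analysis. The landmark discards early deaths in both groups. The screening-based comparison is less specific to stunning because it includes dysfunction that proves persistent.
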